### Interventions

2.4

Endovascular coiling or surgical clipping will be performed once for each patient in treatment group or control group, respectively.

In the treatment group, the patient is under general anesthesia, and the whole procedure is performed under fluoroscopic imaging guidance. An arterial sheath and angiography catheter are inserted through the femoral artery to assess the shape, size, and location of the aneurysm. An appropriate guiding catheter is inserted and advanced to a site close to the aneurysm. According to the angle of the aneurysm and the artery bearing the aneurysm, a microcatheter is inserted through the initial catheter. When the microcatheter has reached the aneurysm and has been navigated into the aneurysm, select an appropriate coil for embolization according to the actual size of the aneurysm.

In the control group, the patient is under general anesthesia. The appropriate surgical approach is selected based on the location of the aneurysm. Make an arc-shaped incision, separate the subcutaneous tissue, drill the skull, mill the bone window, and expose the aneurysm. Determine the artery bearing the aneurysm, and place a clip on the neck of the aneurysm to close the base of the aneurysm.

### Outcome measures

2.5

The primary outcomes are mRS, overall mortality rate, disability rate, morbidity rate, occurrence of a major aneurysm recurrence measured at 6 month and 1 year. The secondary outcomes are occurrence of failure of aneurysm occlusion, intracranial hemorrhage during the treatment, length of hospitalization after the treatment. All related complications and adverse events will also be recorded.

### Sample size

2.6

With alpha 0.05, power 80%, loss to follow-up 20%, and the estimated 18% and 30% of poor clinical outcome rates at 6-month follow-up for endovascular coiling and surgical clipping respectively, a sample size of 450 will be needed.

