### Randomization and blinding

2.3

Parallel-group randomization (1:1) is generated through the random number generator in Microsoft Excel 2010. In this trial, blinding to patients, physicians, and outcome assessors is not possible.

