### Statistical methods

2.7

The χ^2^ test and Fisher exact test will be applied to categorical variables, and Student *t* test, Wilcoxon rank-sum test, or Mann–Whitney *U* test after normality test for mean values. All analyses will be conducted using SPSS version 22 (IBM, Chicago), and *P* < .05 is considered statistically significant.

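### The sample size rests on a 6-month poor clinical outcome that the outcome list neither names nor defines, so the stated power cannot be assigned to any listed primary outcome

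*Protocol article*

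**What the plan says.** Section 2.6 (Sample size) gives its inputs as "With alpha 0.05, power 80%, loss to follow-up 20" per cent, with "the estimated 18% and 30% of poor clinical outcome rates at 6-month follow-up" for coiling and clipping respectively, and concludes that "a sample size of 450 will be needed". The calculation therefore compares two proportions at one visit.

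Section 2.5 (Outcome measures) says: "The primary outcomes are mRS, overall mortality rate, disability rate, morbidity rate, occurrence of a major aneurysm recurrence", all at 6 months and 1 year. It continues: "The secondary outcomes are occurrence of failure of aneurysm occlusion, intracranial hemorrhage during the treatment, length of hospitalization after the treatment". Neither list contains a poor clinical outcome.

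Section 2.7 (Statistical methods) gives tests for categorical variables and for means. It sets one threshold, under which P < .05 "is considered statistically significant". It does not say which test applies to mRS, and it ranks no outcome above another.

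**The concern.** The outcome used to size a trial should be recognisable among its primary outcomes. Here it is not. *Poor* could mean mRS above some cut, disability alone, disability or death, or morbidity. These are different outcomes and can have different event rates, and Section 2.5 lists mRS, mortality, disability and morbidity separately.

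Two things are at stake. A reader cannot tell which result decides the trial or what it was powered to detect. In addition, with five primary outcomes at two visits under one unadjusted threshold, and no definition of the sizing outcome, the article leaves open which comparison becomes the headline. Section 2.3 says outcome assessors cannot be blinded. That does not cause the problem, but it makes an early and fixed definition more valuable.

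**Working it through.** **Step 1: set the two sections side by side.**

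| | Section 2.5 | Section 2.6 |
|---|---|---|
| Outcome | mRS; mortality; disability; morbidity; major recurrence | poor clinical outcome |
| Number | five | one |
| Time | 6 months and 1 year | 6 months |
| Form | a scale (mRS) and four event outcomes | two proportions |

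Five outcomes at two visits make 5 × 2 = 10 outcome-by-time comparisons, and Section 2.6 points to none of them by name. The only mRS threshold in the article is in Section 2.2, where a baseline score of 4 or more is an exclusion. It defines no outcome.

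**Step 2: try to reproduce 450.** Inputs from Section 2.6: p1 = 0.18, p2 = 0.30, alpha 0.05, power 80%, loss 20%. Section 2.3 gives the allocation: "Parallel-group randomization (1:1) is generated". Sidedness is not stated, so two-sided is assumed. The mean rate is (0.18 + 0.30)/2 = 0.24.

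n per arm = [1.960 × √(2 × 0.24 × 0.76) + 0.842 × √(0.18 × 0.82 + 0.30 × 0.70)]² / 0.12²

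= [1.960 × 0.604 + 0.842 × 0.598]² / 0.0144 ≈ 197.7, rounded up to 198.

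The evaluable total is 2 × 198 = 396. Allowing for loss, 396/0.80 = 495, or 496 with equal arms. Other conventions:

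| Method | Evaluable | Divided by 0.80 | Multiplied by 1.20 |
|---|---|---|---|
| Two-sided, pooled | 396 | 495 (496) | 476 |
| Two-sided, continuity-corrected | 428 | 535 (536) | 514 |
| Two-sided, unpooled | 390 | 488 | 468 |
| Two-sided, arcsine | 394 | 494 | 474 |
| One-sided, pooled | 312 | 390 | 375 (376) |
| One-sided, continuity-corrected | 344 | 430 | 413 (414) |

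Figures in brackets are for equal arms. None of these lies within 3% of 450 (437 to 463).

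**Step 3: power that 450 gives for the sizing outcome.** After loss, 450 × 0.80 = 360, or 180 per arm.

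z = (0.12 × √180 − 1.960 × 0.604) / 0.598 = (1.610 − 1.184) / 0.598 ≈ 0.713, so power ≈ 76.2%.

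With no loss at all (225 per arm), power is 84.9%.

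**The case against.** The best defence is that the link is easy to guess. mRS and disability rate are both listed at 6 months, the visit used in Section 2.6, and a dichotomised mRS is a plausible reading. The exact cut is also something that a journal article may leave to the full protocol or analysis plan, neither of which is shown.

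Much of this stands, and it limits the point. A reader might infer that no listed primary outcome has the stated power. The article cannot show that, because one of them may be the intended outcome. Nor do the two sections describe different trials: the arms and the 6-month visit agree. A reader might also be tempted to quote much lower power for rarer outcomes such as death. That would need event rates and treatment effects that the article does not give. Even the direction is uncertain for recurrence, since the Introduction reports more rebleeding after coiling. Finally, a scale analysis of mRS is not shown to have low power; its power is simply not what Section 2.6 calculates.

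The mismatch between two stated sections survives. Omission of a cut could be condensation. Sizing on an outcome that is absent from a full list of five primary and three secondary outcomes is not. A later document that supplied the definition would be choosing the primary outcome rather than elaborating one already stated.

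**Conclusion.** The point holds in this form: the stated power is not tied to any listed primary outcome or time point, and all five primary outcomes share P < .05 without a rule for which one decides. This is an inconsistency between Sections 2.5 and 2.6. It is not proof that no link was intended.

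The one size that can be given concerns the sizing outcome itself: about 76% power rather than 80%. This assumes a two-sided 0.05 test without continuity correction, 20% loss in each arm, and true rates of 18% and 30%. A one-sided 0.05 test would need only 390 and so would exceed 80% with 450, but the article does not state one. The shortfall is separate from the missing definition. It matters here because tying Section 2.6 to a named outcome while keeping 80% would endorse a figure that the inputs do not support.

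**What to change.** **Section 2.5.** Name one primary outcome at 6 months: the binary poor clinical outcome to which the 18% and 30% refer. State its definition and fix it before any outcome data are examined. An mRS cut with death counted as poor would serve if that is how the rates were estimated; the article does not establish any particular cut. The definition must allow for Section 2.2, which excludes only baseline mRS of 4 or more. Patients with a score of 3 can enter, and a cut at 3 would count them as poor from the start. Report the comparison as a risk difference with a 95% confidence interval. Move the other listed outcomes and the 1-year time point to secondary. If the sponsor prefers 1 year as primary, given the stated long-term aim, Section 2.6 must be redone with 1-year rates.

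**Section 2.6.** State that the power applies to this outcome only. Give sidedness, and restate the power as about 76% (two-sided 0.05, 180 per arm after 20% loss). Should 80% be required, the same inputs need about 496 randomised, which is 46 more than planned.

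**Cost.** A few sentences, plus tracing the definition behind the two assumed rates. No new measurement is needed if the definition uses mRS, which is already recorded at both visits.

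### On the plan's own inputs, 450 patients with 20% loss give about 76% power for 18% versus 30%, not the stated 80%

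*Protocol article*

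**What the plan says.** The whole justification of the trial's size is one sentence in Section 2.6 (Sample size) of the protocol article. Its inputs are "With alpha 0.05, power 80%, loss to follow-up 20%, and the estimated 18% and 30% of poor clinical outcome rates at 6-month follow-up" for coiling and clipping respectively, and its conclusion is that "a sample size of 450 will be needed".

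Two other sections supply the rest. Section 2.3 gives the allocation: "Parallel-group randomization (1:1) is generated through the random number generator in Microsoft Excel 2010". Section 2.7 gives the analysis: the chi-square "test and Fisher exact test will be applied to categorical variables", with significance at P < .05. The article does not state whether the test is one- or two-sided, which sample-size formula was used, or which of the two named tests applies to the 6-month outcome.

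**The concern.** Section 2.6 gives every input of a two-proportion calculation except sidedness, so its result can be checked directly. The stated total looks too small once the plan's own 20% loss is taken off.

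The stated power governs how a null result will be read. If it is overstated, a non-significant comparison of coiling with clipping will be credited with a type II risk of 20% when the design carries about 24% (100% − 76%). Nobody checking the protocol can recover 450 from the inputs printed beside it.

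**Working it through.** **Inputs**

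- Poor-outcome rates p1 = 0.18 (coiling) and p2 = 0.30 (clipping), difference 0.12; alpha 0.05; power 80%; loss 20%; total 450 (all Section 2.6).
- Allocation 1:1 (Section 2.3).
- Chi-square or Fisher's exact test at P < .05 (Section 2.7).
- Assumption: two-sided test, so z = 1.960 for alpha and 0.8416 for power. One-sided results are given below.

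**Step 1: number needed**

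With mean rate 0.24, the pooled formula per arm is

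n = [1.960·√(2·0.24·0.76) + 0.8416·√(0.18·0.82 + 0.30·0.70)]² / 0.12²

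= [1.960·0.6040 + 0.8416·0.5980]² / 0.0144

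= (1.1838 + 0.5033)² / 0.0144 = 197.7, so 198 per arm.

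Evaluable total: 2 × 198 = 396. Allowing for 20% loss: 396/0.8 = 495. With equal arms, 198/0.8 = 247.5 rounds up to 248 per arm, or 496. The plan's 450 is 45 short of 495, and 45/495 = 9%.

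**Step 2: attempts to reproduce 450**

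The unadjusted methods are pooled, unpooled, 2·p̄·q̄ and arcsine. The table gives totals.

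| Approach | Unadjusted | Continuity-corrected |
|---|---|---|
| Two-sided, divided by 0.8 | 488–498 | 530–540 |
| Two-sided, multiplied by 1.2 (incorrect inflation) | 468–478 | 509–519 |
| Two-sided, no loss allowance | 390–398 | 424–432 |
| One-sided, divided by 0.8 | 385–393 | 428–435 |
| One-sided, multiplied by 1.2 | 370–377 | 411–418 |

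None gives 450. The nearest values are 435 below and 468 above.

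**Step 3: power the design has**

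450 × 0.8 = 360 evaluable, or 180 per arm. By the normal approximation,

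z = (0.12·√180 − 1.1838)/0.5980 = (1.6100 − 1.1838)/0.5980 = 0.713, so power is 76.2%.

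Exact enumeration over the two binomial distributions at 180 per arm gives:

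- uncorrected chi-square: 76.7%
- continuity-corrected chi-square: 72.4%
- Fisher's exact test: 72.6%

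**Step 4: what would make 80% true with 450**

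- Loss of at most 1 − 396/450 = 12% (uncorrected chi-square). With continuity correction, which is close to Fisher's test, 428 evaluable are needed, so loss could be at most 1 − 428/450 = about 5%.
- Or, at 20% loss, a slightly larger effect: 30% versus about 17.5% instead of 18%.
- With no loss at all (225 per arm), power would be 84.9% by the normal approximation, or 82.3% with Fisher's test.

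**The case against.** The strongest objection is sidedness. The protocol says only alpha 0.05. With a one-sided 0.05 test, power at 180 per arm would be 84.9%, so 450 would be more than enough. The conclusion therefore depends on a two-sided reading, and the correction should state that reading openly. It does not rescue the sentence, however. Nothing in the protocol declares a one-sided test, a one-sided test sits poorly with an introduction that calls the choice between clipping and coiling unsettled, and the one-sided formulas do not give 450 either.

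Two further objections stand in part:

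- **The Fisher figure is the less likely case.** Fisher's test is usually kept for sparse tables. Here the expected poor outcomes are 180 × 0.18 = 32.4 and 180 × 0.30 = 54, so no cell is sparse. The fair headline is 76–77%. The lower figure stays possible because Section 2.7 gives no rule for choosing between the tests.
- **The shortfall is modest.** The rates and the loss are themselves estimates, half a percentage point in the coiling rate would close the gap, and neither bias nor type I error is affected. This limits the harm but does not make the stated power correct.

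A journal article may leave its formula and software to a fuller document, and an unlisted method might lie behind 450. That excuses an omission. It does not excuse a stated result that disagrees with the inputs in the same sentence, and the power at 180 per arm does not depend on how 450 was obtained.

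**Conclusion.** The concern holds. On the plan's own rates, alpha, loss and allocation, and with a two-sided test, 450 randomised patients give about 76% power (76.2% by approximation, 76.7% exact, uncorrected chi-square) instead of 80%. With Fisher's exact test the figure is about 73%. The inputs imply 495 randomised, so the stated number is 9% low. The error is of moderate size and the trial is not grossly underpowered. It still needs correcting, because this is the only justification given for the trial's size and the power it claims is not the power the design has.

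**What to change.** Rewrite Section 2.6 so that number, loss and power agree. Suggested wording:

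> With two-sided alpha 0.05 and 450 patients randomised 1:1, a 20% loss to follow-up leaves 360 evaluable patients and about 76% power to detect poor-outcome rates of 18% versus 30% at 6 months with the uncorrected chi-square test; power is 80% if loss is 12% or less.

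The authors should confirm that two-sided is what they intend, since the present text does not say so. Naming the uncorrected chi-square test for this endpoint matters because the 76% and 12% figures apply only to that test.

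If 80% power at 20% loss is to be kept, the total must instead be 495, or 496 with equal arms.

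The restatement costs one sentence and a slightly less favourable power figure, and needs no extra patients. The alternative costs 45 or 46 more patients.

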### Statistical methods

2.7

The χ^2^ test and Fisher exact test will be applied to categorical variables, and Student *t* test, Wilcoxon rank-sum test, or Mann–Whitney *U* test after normality test for mean values. All analyses will be conducted using SPSS version 22 (IBM, Chicago), and *P* < .05 is considered statistically significant.

## Discussion

3

Most IAs are clinically silent, and the rupture is unpredictable and associated with hematoma and hemorrhage. With the ongoing advances and widespread use of imaging techniques, the possibility to detect asymptomatic aneurysm has increased significantly.^[17]^ The etiology of IA has not yet been clearly defined, and it is mainly believed to be related to congenital arterial wall defects, increased intravascular pressure, atherosclerosis, and vasculitis.^[18,19]^ Treatment of unruptured IAs is still being discussed. Endovascular therapy has become the main method for the treatment of UIA with the advantages of low fatality and disability rate.^[20–23]^ However, it is still controversial about the choice of endovascular coiling because the long term outcomes are still in debate.^[14,15]^ In order to be helpful for the choice of endovascular coiling or surgical clipping, we try to conduct the study to assess the long term efficacy and safety of both operations against UIA. Additionally, this research includes only patients in 1 hospital in China, and the conclusions will be more limited to Chinese people. And the not applicable blind method will also lead to certain biases for the results.
